### Assignment of interventions: allocation

#### Sequence generation {16a}

The study participants will be assigned to the groups using a simple, not stratified randomization of a 1:1 ratio. The randomization list will be generated by an independent data technician using Excel Microsoft prior to the inclusion.

#### Concealment mechanism {16b}

The randomization numbers will be stored in sealed individual envelopes that will be opened in front of the participants.

#### Implementation {16c}

The randomization list will be generated by a data manager non-involved in the study.

### Assignment of interventions: blinding

#### Who will be blinded {17a}

All the participants will be aware of the drug regimen they will be assigned to. But the statistician will be blinded for the analysis to avoid any bias.

#### Procedure for unblinding if needed {17b}

Not applicable. The study team and the participants themselves will all be aware of the arms where participants will be included.

### Data collection and management

#### Plans for assessment and collection of outcomes {18a}

Pregnant women fulfilling the inclusion/exclusion criteria will be recruited during ANC in the study site over a period of about 20 months. Data will be entered by the MDs in paper CRF designed by the study site in accordance to variables to collect over the participants’ visits during the study. Later, data managers will be in charge to enter the data collected in papers in the electronic database. To ensure the accuracy of the process, source data verification of every entry will be performed by the study supervisors before the validation of the database.

At every scheduled and unscheduled visit, the study team will collect vital signs, blood pressure, weight, data on the medical history since the last visit (including any treatment taken), information on any AE, and current signs and symptoms (if any). At the same time, the team will collect blood samples for malaria diagnosis (us-RDT, thick and thin blood film), Hb, and dried blood spots for PCR.

The outcome of pregnancy, birth weight, APGAR score, and maternal Hb will be collected as soon as possible after delivery. Dried blood spots will be collected on placental blood. The newborn will be examined for congenital abnormalities. Both the mother and the newborn will be reassessed at day 28.

##### Demographic data and medical history

Demographic data and a general history of past and/or present illnesses, the medical history since the last visit (including any treatment taken), information on any AE, and current signs and symptoms (if any) will be recorded.

##### Physical and clinical examination

Vital signs (body temperature, pulse rate), blood pressure, and weight will be measured.

An obstetrical examination will be performed and the fetal viability will be recorded.PCR

Bloodspots of 50 μl will be collected on filter paper (Whatman grade 3) at each visit and subsequently every time a blood slide is done. Samples will be used to determine sub-microscopic parasitemia.Malaria diagnostic

In addition to an us-RDT detecting circulating *P. falciparum* antigens, thick and thin blood films will be prepared, dried, and stained with Giemsa according to standard operating procedures (SOP).

If positive, the parasite density (PD) will be calculated by counting the number of *P. falciparum* parasites per 200 leukocytes based on the actual number of WBC/μl. In case this information is missing, the PD will be estimated assuming WBC of 8000/μl. The PD per microliter will be calculated using the following formula:

$$\mathrm{Parasites}/\mathrm{\mu}\mathrm{l}(\mathrm P/\mathrm{\mu}\mathrm{l})=\frac{\mathrm{Number}\;\mathrm{of}\;\mathrm p\mathrm a\mathrm r\mathrm a\mathrm s\mathrm i\mathrm t\mathrm e\mathrm s\;\mathrm c\mathrm o\mathrm u\mathrm n\mathrm t\mathrm e\mathrm d\times8,000}{\mathrm N\mathrm u\mathrm m\mathrm b\mathrm e\mathrm r\;\mathrm o\mathrm f\;\mathrm l\mathrm e\mathrm u\mathrm k\mathrm o\mathrm c\mathrm y\mathrm t\mathrm e\mathrm s\;\mathrm c\mathrm o\mathrm u\mathrm n\mathrm t\mathrm e\mathrm d}$$

The thin smear will be examined for species determination.

Blood smears will be independently read by 2 qualified microscopists and the mean of the PD will be used in the study. Further details are described and explained in the SOP (SOP: quality control (QC) guidelines for the laboratories participating in the study).

### Plans to promote participant retention and complete follow-up {18b}

Participant’s visits are scheduled on monthly basis. In case of a missing visit, the site clinicians will be in charge to phone the participants to enquire for the reason of the missing visit and encourage them to come to the study site. In case participants cannot be reached by phone, a community health worker will be visiting the households for enquiring and encourage participants to come to the study site. In case participants are not reachable, they will be considered as lost to follow-up after 3 missing visits and all attempts to reach out to them will be documented.

In case of loss to follow-up, all the data collected during the woman participation in the study will be used for the analysis. However, in case of consent withdrawal, the participant data will not be used for the analysis.

### Data management {19}

#### Data management and storage

Data management will be handled by the University of Kinshasa which has the required expertise in data management of clinical trials and epidemiological studies.

Data entry and review will be performed following the Data Entry Guidelines and the Data Management plan. Besides this central management, two monitoring visits are planned to check the information entered into the electronic CRF against the source documents available on site. Any modification done onto the electronic CRF will be automatically registered. The final database will be obtained after the resolution of all queries and will be locked for statistical analysis to be carried out according to a pre-established data analysis plan that will be developed by a statistician and submitted for comments and advice to the Trial Steering Committee (TSC).

Every patient will have a personal source document file. Data will be collected onto the source document and entered later in an electronic CRF. Data will be entered on a daily basis on the database.

Study documents will be archived for 10 years and granted to the sponsor for trial-related monitoring, audits, DSMB, and Ethical Committee review and regulatory inspections when applicable.

### Confidentiality {27}

Collected personal information will be restricted to meet the objectives of the study. Prior to the study start, all study staff will sign a confidentiality agreement form. Every participant will be assigned a unique study identification code and no name or personal information will appear in the database or will ever be published. All personal information mentioned in the signed informed consent forms and other documents will be kept under lock and will only be available to the project coordinator and data managers. Information stored in the database will be protected by unique usernames and passwords, which will only be available to minimum appropriate authorized personnel.

### Plans for collection, laboratory evaluation, and storage of biological specimens for genetic or molecular analysis in this trial/future use {33}

For this study, the laboratory analysis carried out will be the Hb dosage using a Hemocue, a diversified evaluation of malaria by TDR, US-TDR, thick and thin smear, and PCR.

Hb assay, TDR, US-TDR, and blood smear will be done on-site. Blood will be taken from a dried blood spot for further PCR analysis. The dried blood spot will be stored in individual zippers, each coded for the study, stored in a dry place and containing silica gel to prevent spoilage.

## Statistical methods

### Statistical methods for primary and secondary outcomes {20a}

#### General analysis principles

Data analysis will be performed after the end of the follow-up period of the last participant included in the study.

Study participants will receive two different interventions depending on which group they are enrolled in. The first group will undergo intermittent screening during pregnancy using ultra-sensitive malaria rapid diagnostic test and treatment with pyronaridine-artesunate—Pyramax® (ISTp-US-Py), and the second group will receive an intermittent preventive treatment as suggested by the NMCP. The analysis will mainly compare the two groups to assess the outcomes of the study. All AEs (severe or non-severe) will be reported in the trial publication and compared in the study arms and gestational weeks. To assess the effect of the study interventions in the IPT and the ISTp arms, we will use the intention-to-treat approach. Meaning that all the participant who has been randomized to an arm or another will be considered as part of that arm for the analysis despite their level of completion.

Data from every woman included with baseline and at least one further visit will be analyzed in the treatment arms to which they were assigned. Safety data from all participants who received at least one dose of the study drug will be used in the analysis to describe AEs. AEs will be grouped by treatment group for the number of events and number of participants with type of event. Descriptive statistics will be summarized by treatment arm and visits.

For all statistics, the confidence intervals will be two-sided and at the 95% level, and the value of *p* < 0.05 will be interpreted as statistically significant.

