#### Intervention description {11a}

The ISTp-US-Py group will comprise pregnant women who will be screened monthly from the beginning of the 2nd trimester with us-RDT and who will be treated with Pyramax® if the test is positive.

Pyronaridine-artesunate (Pyramax®, Shin Poong Pharmaceutical Company, South Korea) is a film-coated tablet containing 180 mg of pyronaridine tetraphosphate and 60 mg of artesunate. As part of the EDCTP2 program supported by the European Union (RIA2017MC-2025-Pyrapreg), Shin Poong (Korea) agreed to donate us treatment for this study as well. The IPTp-SP group will be pregnant women who will receive SP as recommended by the National Malaria Control Program (NMCP) at weeks 16, 28, 32, and 36 of their pregnancy. SP (Fansidar®, Roche Laboratories, Switzerland) is a drug used for the treatment of uncomplicated malaria in children and adults and for IPTp. Fansidar is presented as scored tablets containing 500 mg of sulfadoxine and 25 mg of pyrimethamine. The drug continues to be beneficial to both mother and baby, even in areas of SP resistance [18].

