#### Adverse event reporting and harms {22}

All AEs, both severe and non-severe, will be collected and reported in the participants’ CRF and in a database. In the event of serious AEs, the study team will report to the national ethics committee and the trial steering committee no later than 48 h after the team becomes aware of the event.

An AE will be defined as any adverse medical event in a subject, regardless of the possibility of a causal relationship. The study team will collect the AEs after the consent is signed and the participant enrolled in the study. If a participant experiences an AE after enrollment but before receiving the study intervention, the event will be reported as unrelated to the study products of investigation.

All AEs occurring after entry and before the end of the follow-up period will be recorded until the end of the AE.

A SAE is any untoward medical event that results in any of the following: life-threatening condition (i.e., immediate risk of death), severe or permanent disability, prolonged hospitalization, or significant danger as determined by the Data Safety Monitoring Board. SAEs occurring after a subject has been withdrawn from the study will not be reported unless the investigators believe the event may have been caused by a study product of investigation. Investigators will determine the relationship between an event and the study drug based on a temporal relationship to the study drug, as well as whether the event is unexpected or unexplained given the subject’s clinical course, previous medical conditions, and concomitant medications.

All AEs, both severe and non-severe, will be collected and reported in the participants’ CRF and in a database. In the event of serious AEs, the study team will report to the national ethics committee and the trial steering committee no later than 48 h after the team becomes aware of the event.

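### The adverse-event set counts only dosed women, so ISTp women who never test positive drop out of what should be a randomised comparison of AEs

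*Protocol article*

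**What the plan says.** All references are to the protocol article.

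- **Who is in the AE analysis** (General analysis principles): "Safety data from all participants who received at least one dose of the study drug will be used in the analysis to describe AEs".
- **What is done with AEs** (same section): "All AEs (severe or non-severe) will be reported in the trial publication and compared in the study arms and gestational weeks". Also: "AEs will be grouped by treatment group for the number of events and number of participants with type of event".
- **How a woman comes to be dosed** (Intervention description {11a}): ISTp women are "screened monthly from the beginning of the 2nd trimester with us-RDT and who will be treated with Pyramax® if the test is positive". IPTp women are due SP at four set gestational weeks, with no test as a condition.
- **Principle for the effect of the interventions** (General analysis principles): intention to treat, so that "all the participant who has been randomized to an arm or another will be considered as part of that arm".
- **Who has AE data** (Adverse event reporting and harms {22}): "The study team will collect the AEs after the consent is signed and the participant enrolled in the study". Collection does not depend on dosing.

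**The concern.** A set of everyone who took at least one dose is a usual safety population when both arms are dosed at entry. Here one arm is a test-and-treat strategy. Its women enter the set only through a positive test after randomisation, and a positive test is linked to fever, anaemia and other illness that is recorded as AEs. The other arm has no such filter.

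Two things are at stake. First, the difference in AE rates between arms mixes any effect of the strategy with the difference between ever-positive and never-positive women. Second, AEs and SAEs in never-positive ISTp women, such as a life-threatening event or a prolonged hospital stay that is not itself a study outcome, are collected but do not enter the comparison. The results are meant to inform national policy for pregnant women, so the safety comparison should be of the two strategies as assigned.

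**Working it through.** **1. The plan's own figures.** The article gives no size for the safety set. The arm size follows from Recruitment {15}: 220 × 1.10 = 242, and 242 / 2 = 121 per arm.

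**2. Who enters the set if the rule is followed literally.**

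| Arm | Condition for a first dose | In the AE set |
|---|---|---|
| IPTp-SP | scheduled, no test | nearly all of 121 |
| ISTp-US-Py | at least one positive us-RDT | 121 × q |

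Here q is the share of ISTp women who are ever us-RDT positive. If the drug in the rule were read as Pyramax alone, the IPTp arm would have no safety set, so that reading does not rescue the sentence.

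**3. Size of the ISTp set.** The article does not give q. Two of its figures can be used as assumptions:

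- Table 2 has 23.4% malaria infection under IST. If that is the share ever positive, 121 × 0.234 = 28.3, so about 28 women are in and about 93 (77%) are out.
- Study setting {9} has 30% prevalence in a similar setting. If that applied at each of the six monthly visits in Table 1, independently, q = 1 − 0.70^6 = 1 − 0.118 = 0.882. Then 121 × 0.882 = 106.8, so about 107 women are in and about 14 (12%) are out.

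These are illustrations, not bounds. With an assumed 5% per screen over three screens, q = 1 − 0.95^3 = 0.143, which leaves about 17 women.

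**4. What the selection does to the AE rates.** Suppose the strategies do not differ in AEs and the same share q is ever positive in both arms. Let the AE risk be r1 in ever-positive and r0 in never-positive women. The dosed ISTp set shows r1. The IPTp arm shows q·r1 + (1 − q)·r0. The spurious difference is

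(1 − q) × (r1 − r0).

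Take r1 = 40% and r0 = 20%, which are assumed values that appear nowhere in the article:

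| q | ISTp, dosed | IPTp | Spurious difference | All randomised |
|---|---|---|---|---|
| 0.234 | 40% | 24.7% | +15.3 points | 0 |
| 0.30 | 40% | 26.0% | +14.0 points | 0 |
| 0.882 | 40% | 37.6% | +2.4 points | 0 |

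With r1 = 30% each difference halves; at q = 0.30 it is +7 points. The sign follows r1 − r0. If never-positive women with missed infections had the higher AE risk, it would reverse.

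**5. Counts can point the other way.** The article plans numbers of participants with each type of event. At q = 0.30 in step 4, the ISTp arm would show 36.3 × 0.40 = 14.5 women with an AE and the IPTp arm 121 × 0.26 = 31.5, although the strategies are identical by construction. Rates would make ISTp look worse, and raw counts would make it look better.

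**The case against.** The strongest reply is that General analysis principles already contains an unrestricted statement: all AEs are reported and compared between the arms, directly before the intention-to-treat sentence. The dosed-only sentence says only that its data serve to describe AEs. On that reading the plan has an all-participant comparison plus a dosed-only description, which is close to what is asked for here. The reading is possible, but the text does not secure it. The dosed-only sentence is the only one that names a population for AE data, the next sentence groups AEs by treatment group, and the intention-to-treat sentence is stated for the effect of the interventions. The two statements need to be reconciled. This is a rule the article states, not a detail left to an analysis plan.

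The other replies limit how far the point goes, and they stand:

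- A reader might infer that the harms of missed infection disappear from the trial. They do not. Malaria is the primary outcome. Anaemia, spontaneous abortion, intrauterine death, preterm birth, low birth weight and neonatal death are secondary outcomes. All are analysed by assigned arm in women with a baseline and at least one further visit, dosed or not.
- A reader might infer that every woman with a false-negative test is left out. The us-RDT is repeated at scheduled and unscheduled visits (Participant timeline {13}), so a woman who later tests positive and is treated enters the set. Only never-positive women stay out.
- A reader might take 23.4% as this trial's positivity at each screen. The note to Table 2 says the figures come from IST with a standard RDT and another drug, and no time basis is given. The share dropped cannot be derived from it.
- No AE endpoint, safety hypothesis or safety sample size is stated, and nothing is irretrievable because AEs are collected from enrolment.

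**Conclusion.** The point holds within those limits. Followed as written, membership of the AE set depends on a post-randomisation positive test in the ISTp arm and on almost nothing in the IPTp arm, while the same section calls for a comparison between arms. That comparison is not randomised, and it omits AEs and SAEs outside the listed outcomes in never-positive ISTp women.

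How many women are dropped is unknown. The figures of about 28 and about 107 of 121 remaining rest respectively on reading 23.4% as the share ever positive and on 30% at each of six independent screens. The spurious differences in AE rates rest on assumed AE risks and show only that the distortion can be material when q is low and is small when q is high. Its direction cannot be settled from the article, so a claim that the set favours or disfavours ISTp would go too far.

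This should be fixed before analysis. It does not bear on the primary non-inferiority conclusion, which concerns malaria status by assigned arm.

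**What to change.** Reconcile the two statements in General analysis principles, and carry the result into the analysis plan, as follows:

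- AEs and SAEs are compared between arms in all randomised women, by assigned arm, from randomisation to end of follow-up. Give the denominator for each arm with every count and percentage.
- The dosed-only set is kept as a supplementary, non-comparative description of AEs after Pyramax and after SP.
- Say how the all-randomised set treats two rules stated elsewhere in the article: data of women who withdraw consent are not used ({18b}), and SAEs after withdrawal from the study are reported only if thought to be caused by a study product ({22}).

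The cost is wording and one extra table. No new data are needed, since AEs are already collected from enrolment in every participant. The article describes the analysis as still to come and the data analysis plan as still to be developed. No clinical rule changes.

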### Secondary objectives

The secondary objectives are to assess that:

During pregnancy:The proportion of asymptomatic/symptomatic malaria cases is not higher when using ISTp-US-Py compared to IPTp-SPThe proportion of the parasite densities is not higher when using ISTp-US-Py compared to IPTp-SPThe proportion of anemia is not higher when using ISTp-US-Py compared to IPTp-SPThe incidence of spontaneous abortions or intrauterine deaths is not higher when using ISTp-US-Py compared to IPTp-SP

At birth:

In women:The proportion of asymptomatic/symptomatic malaria cases is not higher when using ISTp-US-Py compared to IPTp-SPThe parasite densities are not higher when using ISTp-US-Py compared to IPTp-SPThe proportion of anemia is not higher when using ISTp-US-Py compared to IPTp-SP

In the offspring including:Intrauterine deathThe fetal morbidities (preterm birth, low birth weight) are not higher when using ISTp-US-Py compared to IPTp-SP

During the 28-day period following the birth:The neonatal and early neonatal mortality of the offspring is not higher when using ISTp-US-Py compared to IPTp-SP

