### Sample size {14}

The calculation of the sample size has performed using the Sealed Envelope Ltd. 2012. Power calculator for binary outcome non-inferiority trial. [Online] Available from: https://www.sealedenvelope.com/power/binary-noninferior/.

Referring to the results of a study comparing IPTp-SP and IST (dihydroartemisinin-piperaquine) [11], the number of participants required to detect a difference of 10% with a significance level of 5% and a power of 80% to assess the non-inferiority of IST to IPTp-SP vary as described in Table 2. Variables of interest considered were the malaria status, the anemia status, and the low birth weight rate.

**Table 2 Tab2:** Variation of the sample size according to the difference of the outcome of interest

	IPTp	IST	Sample size
Low birth weight	10.5	15.7	122
Malaria infection	18.9	23.4	196
Anemia	30	25	220

*NB*: IST with dihydroartemisinin-piperaquine and standard RDT was used as an example to calculate the sample size for the current study as there are no previous studies could be found that include assessment of Pyramax® and us-RDT for use as IST.

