### Recruitment {15}

Based on the assumption described above, a total of two hundred and twenty pregnant women is the minimal sample size required to answer our research question. However, anticipating on a non-compliance and/or loss-to-follow-up rate of 10%, the adjusted total sample size required will be 242 pregnant women (121 participants per arm).

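### The sample size rests on one-sided 5% but the analysis fixes two-sided 95% intervals, so the anaemia calculation that sets the trial size has 70–74% power, not 80%

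*Protocol article*

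**What the plan says.** Under Sample size {14}, the protocol article cites a "Power calculator for binary outcome non-inferiority trial". It describes the planning target as "the number of participants required to detect a difference of 10" per cent. The error rates that go with this target are set out as "with a significance level of 5% and a power of 80% to assess the non-inferiority of IST to IPTp-SP". Whether the 5% is one- or two-sided is not stated. Table 2 lists three outcomes with IPTp rate, IST rate and total; its largest total is the row "Anemia 30 25 220", and the row for the primary outcome is "Malaria infection 18.9 23.4 196".

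Recruitment {15} takes 220 as the minimum, allows 10% for non-compliance or loss, and concludes that "the adjusted total sample size required will be 242 pregnant women (121 participants per arm").

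General analysis principles sets the inferential standard: "For all statistics, the confidence intervals will be two-sided and at the 95% level, and the value of" *p* < 0.05 is to be read as statistically significant. The 10-point difference does not reappear in the statistical methods. The sections on interim and additional analyses say only that non-inferiority will be assessed. The secondary objectives are worded as absence of increase, for example: "The neonatal and early neonatal mortality of the offspring is not higher when using ISTp-US-Py compared to IPTp-SP".

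**The concern.** A non-inferiority conclusion drawn from a two-sided 95% interval uses only one of its limits, so it is a test at one-sided 2.5%. If the sample size was computed at one-sided 5%, the trial is sized for a weaker standard than the one it says it will apply, and the stated 80% power is not delivered. This affects the anaemia row in particular. That row fixes the total, and it is the only one of the three whose assumed rates favour ISTp.

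There is also a gap in the link between sizing and analysis. The figure that acts as the margin appears only in the sample size section, while the one stated criterion in the analysis section is a significance threshold without a margin. Results are meant to inform national prevention policy, so the rule for declaring non-inferiority, and the real chance of meeting it, should be readable from the protocol.

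**Working it through.** **Inputs.** From Sample size {14}: difference of 10 points, taken as the margin; 5% level; 80% power; Table 2 rates. From Trial design {8}: 1:1 allocation. From Recruitment {15}: 220 evaluable, 242 with the loss allowance.

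**Formulas** (unpooled variance; C = IPTp, T = ISTp; adverse outcome):
- V = pC(1−pC) + pT(1−pT)
- distance D = 0.10 − (pT − pC)
- n per arm = (z(1−α) + 0.842)² × V / D²
- power = Φ(D/SE − z(1−α)), with SE = √(V/n)

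(1.645 + 0.842)² = 6.18 at one-sided 5%; (1.960 + 0.842)² = 7.85 at one-sided 2.5%.

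**Step 1: reproduce Table 2.**

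| Row | V | D needed | n per arm and total, one-sided 5% | n per arm and total, one-sided 2.5% | Stated total |
|---|---|---|---|---|---|
| Low birth weight | 0.2263 | 0.152 | 60.6 → 61; 122 | 77; 154 | 122 |
| Malaria | 0.3325 | 0.145 | 97.8 → 98; 196 | 125; 250 | 196 |
| Anaemia | 0.3975 | 0.150 | 109.2 → 110; 220 | 138.7 → 139; 278 | 220 |

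All three totals match exactly at one-sided 5% and none at one-sided 2.5%. The anaemia distance is correctly signed: 0.10 − (0.25 − 0.30) = 0.15. The other two rows match only if the higher IST rate is counted as a benefit (0.10 + 0.045 and 0.10 + 0.052). With the outcome taken as adverse, the malaria distance is 0.10 − 0.045 = 0.055.

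**Step 2: anaemia power on the stated interval.**
- 110 per arm: SE = √(0.3975/110) = 0.0601; 0.15/0.0601 = 2.495. One-sided 5%: Φ(0.850) = 80%. Two-sided 95% interval: Φ(0.535) = 70.4%.
- 121 per arm: SE = 0.0573; 0.15/0.0573 = 2.617. One-sided 5%: Φ(0.972) = 83%. Two-sided 95% interval: Φ(0.657) = 74.4%.

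**Step 3: malaria power, outcome taken as adverse.**
- 110 per arm: SE = √(0.3325/110) = 0.0550; 0.055/0.0550 = 1.000. One-sided 5%: Φ(−0.645) = 26%. Two-sided 95% interval: Φ(−0.960) = 17%.
- 121 per arm: 28% and 18%.

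**Step 4: loss allowance.** 220 × 1.10 = 242, but 242 × 0.9 = 217.8, below the stated minimum of 220. Dividing instead, 220/0.9 = 244.4, or 246 in equal arms; this holds at the planning alpha only. The effect is negligible: with 217.8/2 = 108.9 per arm, anaemia power at one-sided 5% is 79.9%.

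**The case against.** The strongest objection concerns the decision rule. A reader might infer that the stated test does not test non-inferiority at all, or that p ≥ 0.05 will be taken as proof that an outcome is no higher. The documents do not support this. The sentence on p-values sits among general principles, names no test, and says only when a result counts as significant; nowhere is a non-significant result equated with non-inferiority. A two-sided 95% interval compared with 10 points would be a valid non-inferiority test, and the power figures above assume exactly that comparison. Data management {19} also defers the analysis to a pre-established plan that is not shown and may contain the rule. What stands is narrower: as written, the p-value criterion is not tied to the 10-point difference.

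Three further points are fair:
- One-sided 5% is inferred, not printed. The inference is strong, since all three rows match exactly and none matches at 2.5%.
- A flat 70% would be too pessimistic. The protocol keeps data from women lost to follow-up and analyses anyone with baseline and one later visit, so the loss may be under 10%. The range 70–74% is the right statement.
- The loss arithmetic is trivial in effect, and enlarging the total is no remedy once recruitment is complete.

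None of these removes the mismatch, which lies between two sections of the article itself and is not a detail left to an analysis plan.

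**Conclusion.** The mismatch is established. The sizing uses one-sided 5% and the analysis uses an interval equivalent to one-sided 2.5%. For anaemia, the row that sets the trial size, power is about 70% with 110 per arm and 74% with 121, against the stated 80%. Reaching 80% on the 95% interval would need 278 evaluable women.

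This rests on the 10% difference being an absolute margin, on Table 2's rates being true, on one binary result per woman, and on the normal approximation with unpooled variance.

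Anaemia is the favourable case. For malaria, the primary outcome, the same sample gives about 17% on the 95% interval and 26% at one-sided 5% (110 per arm, Table 2's rates taken as adverse). That shortfall comes mainly from the direction in which the malaria row was computed, not from the choice of alpha, but any power statement that omits it would mislead.

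**What to change.** Recruitment is complete, so this is a change of wording, to be recorded before the database is locked.

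1. **Use one alpha in Sample size {14} and General analysis principles.** Either keep the two-sided 95% interval and restate anaemia power as 70–74%, or state that non-inferiority is judged at one-sided 5%, with a two-sided 90% interval, which keeps about 80% for anaemia.
2. **Tie the interval to the margin.** State in the analysis section that non-inferiority is concluded only if the upper limit of the chosen interval for the ISTp minus IPTp risk difference is below 10 percentage points. Add that a non-significant p-value is not evidence that an outcome is no higher.
3. **Disclose malaria power beside that rule:** about 17% on the 95% interval or 26% at one-sided 5%, with 110 per arm and Table 2's rates taken as adverse.
4. **Note the loss arithmetic** (242 × 0.9 = 217.8) without changing the recruited total.

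No new data or visits are needed. Under the first option in item 1 the stated anaemia power falls; under the second, the chance of a false non-inferiority claim at the margin is 5% instead of 2.5%, and this should be said openly. Either way the disclosed malaria power is low.
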